### Study setting

This trial was be conducted in 4 maternity wards in three cities across the Province of Québec, each located in distinct geographical regions: Sherbrooke in the Eastern Townships: the CIUSSSE-CHUS; Montreal: CHU (Centre Hospitalier Universitaire) Ste-Justine and the McGill University Health Centre; Québec city: the CHU de Québec/CHUL. These four sites were selected based on the fact that they collectively serve over 20% of the province’s population and are representative of its ethnic diversity.

### Eligibility

Mothers were deemed eligible to participate if their child was born in one of the participating maternity wards. In the case partners were present at the maternity ward, they were also invited to receive the intervention and be involved with the mothers in assessing the study tools. For the Sherbrooke site, inclusion was limited to mothers living in the Eastern Townships region. For the Québec City site, inclusion was limited to mothers living in the Capitale-Nationale region. Mothers were excluded if < 18 years, if they do not speak either French or English, or should the child presented an unstable condition requiring intensive care management, or should interview be in any way incompatible with the mother’s health.

### Patient involvement

This trial was designed taking into account results from satisfaction survey completed by mothers enrolled in the PromoVac study [32].

### Enrolment

The maternity ward medical staff made initial contact with and ascertained potential study participants during daytime (8 AM to 5 PM) on week days (Monday to Friday). This was done on the day following childbirth, except when that day fell on a Saturday or Sunday. Only when the prospective study participant agreed to meet with the study research assistant, were the project participation details presented. Written informed consent was obtained from each participant prior to starting study participation. To protect identity and privacy, participants were identified by a code number and the code key linking participant’s identity and research file were kept safely by the study investigator during 10 years. Randomization was secured by the research assistant.

### Intervention

Because infant vaccination starts at 2 months of age, it seems appropriate to promote vaccination to mothers very early during their newborn life. Accordingly, maternity wards seemed to offer a convenient setting, as 98% of all Québec infants are born there [33]. Importantly, our feasibility study confirmed that over 85% of families consider the maternity ward an appropriate setting to discuss infant vaccination. Indeed, 97% of study participants confirmed that they would recommend this strategy to other families [32]. Therefore, we established the maternity ward as a key location to dispense the MI-based intervention.

#### Intervention arm

The proposed study intervention integrates concepts of the MI and Prochaska’s stages of change [34]. The MI is a brief intervention style, using a directive approach to help an individual come to a decision and find the internal motivation to modify its behavior. The MI is based on empathy, the absence of argumentation, the nonjudgmental exploration of ambivalence, and the respect of a person’s autonomy [29]. Motivation is the probability that a person will start, pursue and adhere to a specific strategy of change. The MI is based on four main principles: 1) empathy, 2) developing a discrepancy between interviewee’s current and desired behavior, 3) dealing with resistance, and 4) empowerment. The goal is to engage that person in a collaborative working relationship, allowing him to feel involved in the decision to change, in a respectful and non-judgmental atmosphere. Counseling based on MI involves five core communication strategies: 1) open-ended questions, 2) affirmative statements, 3) reflective listening, 4) careful summarization, and 5) informing and advising only when prior permission was expressly given by the interviewee to do so. Prochaska and DiClemente’s trans-theoretical stages of change model [34, 35] is a behavioral approach model. It typically features five stages over the course of behavioral change: 1) pre-contemplation, 2) contemplation, 3) preparation, 4) action and 5) maintenance (Fig. 1). In order to mobilize mothers to vaccinate, it is important to welcome them at their own respective stage regarding their current intention toward infant vaccination. The aim of the MI-based intervention is to help bring the mother to a forward stage, rather than to the final decision to vaccinate. It is fundamental to keep in mind that, for many mothers, coming to a change of opinion on vaccination is a difficult process.

**Fig. 1 Fig1:**
[figure not shown]
Prochaska’s Stages of Change

The MI-based intervention covers five main areas: 1) the six diseases targeted by vaccination at 2, 4 and 6 months and their consequences; 2) vaccines and their efficacy; 3) the importance of the immunization calendar at 2, 4 and 6 months; 4) the reluctance to vaccinate and vaccination side-effects, based on the tool developed by the Centers for Disease Control and Prevention (CDC) National Immunization Program and the Frequently Asked Question section of the Quebec Immunization Protocol [36]; and 5) local vaccination services and facilities in each of the study regions.

#### Standardization

The intervention was delivered in a standard manner at all of the four participating study sites, by different research assistants at each site. A standard operating procedures manual was prepared to support research assistants’ training. This manual is a compendium of factual information about vaccines delivered to infants aged 0 to 6 months with a great attention to adapt those information in a easily and understandable way for mothers. The manual data were collected from the Quebec Immunization Protocol [36] and the Canadian Paediatric Society [37], on infant vaccines that protect against diphtheria, tetanus, poliomyelitis, whooping cough, and *Haemophilus influenzae* type b, hepatitis B, pneumococcal and rotavirus infections. Each research assistant also received the same validated training session on MI techniques. Prior to starting the study, a two-week run-in phase was conducted at each participating maternity ward in order to identify potential facilitators, obstacles and barrier(s) to implementation. During this run-in phase, the assistant coordinator and the research assistant at each participating site validated the use, under real-life conditions and situations, of the MI techniques.

For purpose of the PromoVaQ Study, we adapted the Prochaska’s trans-theoretical stages of change model taking into account the alternate positions that mothers adopt with respect to infant vaccination. Prior to the MI-based intervention, the research assistant assessed with each mother her current intention to vaccinate. “Undecided” mothers were categorized as either: a) resistant to vaccination (pre-contemplation stage) or b) open but hesitant toward vaccination (contemplation stage). “Committed” mothers were categorized as either: a) deciding to vaccinate (preparation stage) or b) mobilizing to vaccinate (action stage). The research assistant accepted mothers’ responses in a nonjudgmental manner and adjusted the MI-based intervention according to each mother’s stage and the modalities described under Fig. 1.

#### Control arm

Participants enrolled in the control arm of the study were provided with a copy of the Public health vaccine brochure handout upon hospital discharge, as per usual care.

### Study outcomes

The primary outcome will be vaccine coverage at 7 months. Secondary outcomes are: 1) vaccine status (complete, incomplete or non-vaccinated) at ages 3, 5, 13, 19, 24 and 36 months; 2) median vaccination age for vaccines recommended at 2, 4, 6, 12 and 24 months; 3) mean number of days under-immunized at 2, 4, 6, 12 and 24 months; 4) maternal intention to vaccinate pre- and post-intervention; 5) maternal vaccination hesitancy score pre- and post-intervention. Independent variables are maternal socio-demographic and clinical characteristics, the perceptions and opinions toward vaccination of families having received the MI-based intervention, and components of the composite model used for the study (Fig. 2).

**Fig. 2 Fig2:**
[figure not shown]
Intervention composite model

### Outcome measurements tools

Vaccine coverage will be calculated from data uploaded from the Eastern Townships public health vaccination registry, the provincial vaccination registry (2016 - onwards) and the postal survey of mothers of children born in Montreal-area maternity wards. To collect data on family beliefs, attitudes and intention to vaccinate, questionnaires were distributed to families pre- and post-intervention. The pre-intervention (Q1) and post-intervention (Q2) questionnaires were elaborated and built according to a composite model (Fig. 2) inspired from the Health Belief Model [38] and the Theory of Planned Behaviour [39]. Both questionnaires were self-administered and validated during the PromoVac study. Answers were provided according to a 4-category Likert scale. Q2 also collected data with respect to maternal satisfaction regarding the MI-based intervention received. Q2 was offered only to mothers having received the MI-based study intervention. Throughout the study, research assistants at each participating maternity kept a record of all implementation barriers and facilitators.

### Study schedule and follow-up scheme

In order to give a reasonable time frame for mothers to have their infants vaccinated as per Quebec’s recommendations at 2, 4 and 6 months of life, the vaccination status of each participating infant was assessed at ages 3, 5 and 7 months. This one-month period is set by the Canadian Network of Immunization registries [8]. Vaccine status is considered “complete” when an infant has received all vaccines and antigens recommended by the Quebec Immunization Protocol. In order to benefit from the most exhaustive data possible, vaccination data of all participating children will be uploaded from the registries at two separate time points i.e. at 10 and 40 months passed the inclusion of the last infant in the study, enabling collection of the 2, 4 and 6 months vaccine data, and next the 13, 19, 24 and 36 months vaccine data. Once the vaccine status of each child will be determined, percentage of vaccine coverages will be calculated for each study population (intervention/control) according to the following formula: the number of infants in the study population (intervention/control) displaying “complete” vaccine status (at 3, 5, 7, 13, 19, 24 and 36 months) divided by the total number of infants in the study population (intervention/control) during the study period, multiplied by 100.

### Sample size

The 2012 survey estimated vaccine coverage was 74% at 7 months for Québec infants [40]. Our hypothesis is that the intervention will improve vaccine coverage by a minimum of 5% raising it to 79% for mothers having received the MI-based intervention at the maternity ward. A total of 1128 participants are needed to detect a significant difference of 5% in vaccine coverage at 7 months of age, with a risk of error α = 0.05, a power of 80% and using a bilateral test. Factoring a 20% rate of attrition, notably for the Montreal-area for which there is no vaccination registry, a total of 2750 mothers were included in this study i.e. 625 from the Montreal-area and Québec city sites, and 875 from the Sherbrooke site, in order to compensate for follow-up losses at both Montreal-area sites.

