## Methods/design

### Design

This pragmatic, unblinded, parallel, randomized, controlled study will compare the impact of a motivational interview (MI) vs the standard of care information leaflet provided to mother of infants born in the past 48 h. The trial recruitment period covered March 2014 to February 2015, with a final outcome measured in 3-year old children. Taking into account the time required to complete data collection and extraction from the appropriate national vaccination and health registries, this trial will be completed in March 2019. Randomization was conducted at the participant/maternal level, using a block size strategy (eight participants/block) to avoid bias. Randomization was stratified by site using a 1:1 allocation ratio to ensure proportionate allocation among sites. Random allocation was investigator-blinded using a web-based system (Dacima Software).

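### The 1128 participants given as the total requirement are the number per arm; a total of 1128 has about 51% power, not 80%, and does not lead to the 2750 enrolled

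*Protocol article*

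**What the plan says.** All the design inputs but one are in the Sample size section of the protocol article. The control rate comes from a survey: "The 2012 survey estimated vaccine coverage was 74% at 7 months for Québec infants". The intervention is expected to "improve vaccine coverage by a minimum of 5% raising it to 79% for mothers having received the MI-based intervention". The error rates are set "with a risk of error α = 0.05, a power of 80% and using a bilateral test". The requirement follows: "A total of 1128 participants are needed to detect a significant difference of 5% in vaccine coverage at 7 months of age".

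The next sentence moves to enrolment: "Factoring a 20% rate of attrition, notably for the Montreal-area for which there is no vaccination registry, a total of 2750 mothers were included". It splits that number by site, with 875 from Sherbrooke and 625 from the others; 3 × 625 + 875 = 2750 if 625 is read as per site.

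The remaining input is in the Design section: "Randomization was stratified by site using a 1:1 allocation ratio to ensure proportionate allocation among sites". Nowhere does the article describe 1128 as a per-group number or give 2256 as a total.

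**The concern.** Detecting a 5-point difference near 75% with 80% power takes well over a thousand participants per arm, so a whole-trial requirement of 1128 looks about half of what is needed. The step to 2750 adds to the doubt: a 20% allowance for loss cannot more than double a sample size.

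This is the only power justification for the primary outcome in the article. Follow-up is also the trial's acknowledged weak point, because the Montreal-area sites have no registry and depend on a postal survey. Someone judging whether follow-up was adequate would take 1128 evaluable infants as enough. A null result with, say, 1500 evaluable infants could then be read as coming from a fully powered comparison when it did not.

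**Working it through.** **Inputs.** p₁ = 0.74, p₂ = 0.79, difference 0.05, two-sided α = 0.05 (z = 1.960), power 80% (z = 0.8416), 20% attrition (all from Sample size); 1:1 allocation (from Design). The mean proportion is (0.74 + 0.79)/2 = 0.765.

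**1. Reproducing the stated figure.** The pooled-variance normal approximation is

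n per arm = [z₁₋α/₂ √(2p̄(1−p̄)) + z₁₋β √(p₁(1−p₁) + p₂(1−p₂))]² / (p₂−p₁)²

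- √(2 × 0.765 × 0.235) = √0.35955 = 0.5996
- √(0.74 × 0.26 + 0.79 × 0.21) = √0.3583 = 0.5986
- 1.960 × 0.5996 + 0.8416 × 0.5986 = 1.1752 + 0.5038 = 1.6790
- 1.6790² / 0.05² = 2.8191 / 0.0025 = 1127.6, so **1128 per arm and 2256 in total**

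The published number is reproduced to the unit, but as a per-arm size.

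**2. Could another method give 1128 as a total?**

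| Method | Per arm | Total |
|---|---|---|
| Pooled, two-sided | 1128 | 2256 |
| Unpooled, two-sided | 1125 | 2250 |
| Arcsine, two-sided | 1126 | 2252 |
| Continuity-corrected, two-sided | 1168 | 2336 |
| Pooled, one-sided | 889 | 1778 |
| Continuity-corrected, one-sided | 928 | 1856 |

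None does. Even the one-sided version, which contradicts the stated bilateral test, needs 1778.

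**3. Power.** With n per arm, power = Φ[(0.05√n − 1.960 × 0.5996) / 0.5986].

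| Scenario | n per arm | Power |
|---|---|---|
| 1128 in total, as stated | 564 | 50.8% |
| 2750 less 20% = 2200 | 1100 | 79.0% |
| 2256 in total | 1128 | 80.0% |
| 2750, no loss | 1375 | 87.2% |

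For 564 per arm: (1.1874 − 1.1752) / 0.5986 = 0.020, and Φ(0.020) = 0.508. With a continuity correction it is 48.0%. At 564 per arm, a rise from 74% to 81% (7.0 points) has 80.5% power, so 7.0 points is about the smallest rise detectable with 80% power.

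**4. The attrition step.**

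| Starting total | Divided by 0.80 | Multiplied by 1.20 |
|---|---|---|
| 1128 | 1410 | 1354 |
| 2256 | 2820 | 2708 |

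Starting from 1128, neither convention comes near 2750; going from 2750 down to 1128 would take a loss of 1 − 1128/2750 = 59%. Starting from 2256, the two conventions bracket 2750. Enrolment of 2750 keeps 2256 infants if the loss is no more than 1 − 2256/2750 = 18.0%.

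**The case against.** The strongest reply is that the trial itself is not underpowered. The 2750 enrolled fit a requirement of 2256, so the planners evidently worked from the right number and one word in an intermediate step is wrong. On that view the 51% describes a trial that nobody planned, recruitment is over, no rule in the article uses 1128 as a threshold, and the consequence is small. This stands as a limit on the finding: the 51% belongs to the stated requirement, not to the trial as enrolled. It does not make the sentence right. The article uses the same phrase, a total, for both 1128 and 2750, so the plain reading is the whole trial, and the stated size does not deliver the stated power.

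A second reply is that 79% after attrition is itself an assumption. The text ties loss notably to the Montreal area, while the other sites have registry follow-up. If, purely for illustration, 20% were lost only at the two Montreal-area sites (1250 mothers, 250 lost), 2500 infants would remain, 1250 per arm, with 83.9% power. Missing data are also to be multiply imputed, so a count of evaluable infants does not fully describe the analysis. Both points are fair. The 79% is conditional on the article's own overall 20% loss and should be worded so. Likewise, 2750 falls short by 70 if one divides by 0.80 but not if one multiplies by 1.20, and the article does not say which it used.

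Third, the earlier regional cohort also had 1128 families (Background), which might suggest a copying slip. The formula returns 1128 per arm without that explanation, and a copied figure would still be wrong as a total.

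**Conclusion.** The concern holds. On the article's own inputs, 1128 is the per-arm size and the total is 2256, so the published requirement is too small by a factor of two. As written it carries 50.8% power against the claimed 80%, and it cannot be carried forward to 2750 with a 20% allowance.

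The enrolled trial is close to its intended power: 79.0% if 20% are lost overall, and 87.2% with complete follow-up. These figures assume the planned 74% and 79%, equal arms, and a simple comparison of two proportions among infants with data. The remaining shortfall after 20% loss is small, 2200 against 2256.

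**What to change.** Correct the Sample size paragraph in three places:

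- State that 1128 participants per arm, 2256 in total, are needed for 80% power.
- Show the step to enrolment: with 20% loss overall, the 2750 mothers enrolled give about 2200 evaluable infants (1100 per arm) and about 79% power. Say that this power rests on a 20% loss across the whole trial.
- Name 2256 evaluable infants as the number against which follow-up is judged, and acknowledge that it is met only if loss stays at or below 18.0%.

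The cost is one rewritten paragraph. No participants are added, and neither the design nor the analysis changes. The only concession is that the stated power after attrition becomes about 79% instead of 80%.

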### Analytical statistical plan

Files containing vaccination data on participants and the questionnaires from each site will be sent to the Institut National de Santé Publique du Québec (INSPQ) for centralized data capture and analyses. Descriptive analyses of answers provided from each of the two study questionnaires will be performed. Primary analyses will be performed under intention to treat, whereas sensitivity analyses will include per protocol analyses. Frequencies and percentages will be presented as categorical variables. Means and standard deviations will be presented for normally-distributed continuous variables. Medians and interquartile ranges will be presented for abnormally-distributed continuous variables. Answers to the pre- and post-intervention questionnaires, notably the trans-theoretical stages of change model components, as well as the intention to vaccinate measured pre- and post-intervention will be compared using the McNemar’s test for categorical variable and Wilcoxon signed-rank test for continuous variable. Pre-intervention intention to vaccinate will then be dichotomized (“Certainly” answers, defined as certain, vs. “Probably”, “Probably not” and “Certainly not” answers, defined as uncertain) and compared by univariate analysis to the other variables as measured pre- and post-intervention. Categorical variables and vaccination intention will be compared using the Khi2 or Fisher exact test (expected frequency < 5). Normally-distributed continuous variables will be compared to intention to vaccinate using Student’s T-test and abnormally-distributed continuous variables will be compared to intention using the Mann-Whitney test. To identify the principal influencing factors on the “certain” intention to vaccinate, a multivariate logistic regression model with a step-by-step method will be used. To avoid co-linearity between the model’s independent variables, only those variables with a univariate *p* < 0,1 and a correlation coefficient < 0,6 (Pearson correlation, Spearman correlation) will be integrated into the multivariate logistic regression model. Co-linearity will be checked for the final model, and model fit will be assessed using the Akaike Information Criterion and the Hosmer and Lemeshow test. The vaccination status of the children will be compared between the intervention and the control groups. Missing data will be handled through multiple imputation techniques. All statistical will be 2-tailed and *p*-values of 0.05 or less will be considered significant.

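### The model of pre-intervention intention to vaccinate admits candidate factors measured after the intervention, which exist in one arm only

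*Protocol article*

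**What the plan says.** All places are in the protocol article.

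- **Outcome.** Under *Analytical statistical plan*: "Pre-intervention intention to vaccinate will then be dichotomized". The top answer counts as certain and the other three as uncertain. No such split is defined for the post-intervention answer.
- **Candidates.** The dichotomized intention is then to be "compared by univariate analysis to the other variables as measured pre- and post-intervention".
- **Model.** The aim is stated as "To identify the principal influencing factors on the “certain” intention to vaccinate", for which "a multivariate logistic regression model with a step-by-step method will be used".
- **Entry rule.** To limit collinearity, "only those variables with a univariate *p* < 0,1 and a correlation coefficient < 0,6" go into the model.
- **Who has post-intervention data.** Under *Outcome measurements tools*: "Q2 was offered only to mothers having received the MI-based study intervention". Here Q2 is the article's name for the post-intervention questionnaire and Q1 for the pre-intervention one.
- **Independent variables.** *Study outcomes* lists among them "the perceptions and opinions toward vaccination of families having received the MI-based intervention", without naming the dependent variable that they are meant to explain.

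**The concern.** The analysis is worded as a search for influences. A factor can influence an intention only if it precedes it. A Q2 answer is given after the pre-intervention intention has been recorded, and the session lies between the two. The plausible direction runs the other way: a mother already certain to vaccinate will tend to give more favourable answers afterwards. Such a variable is likely to be associated with prior intention and so to pass a p<0.1 screen, but it is not a determinant.

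There is also a structural problem. Controls have no Q2 by design, so one retained Q2 term changes the population on which the whole model is fitted.

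At stake is the account of what drives intention to vaccinate. The abstract names psychosocial determinants of intention among the secondary outcomes, and the *Discussion* intends the trial's results for the ministry and immunization committees.

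**Working it through.** The article gives no figure to reproduce for this analysis. The check is mainly a reading of the text, with two small illustrations.

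**1. Follow the rule as written.**

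| Step | What the article fixes | Consequence |
|---|---|---|
| Outcome | Pre-intervention intention, two categories | Recorded before the session |
| Screen | Variables from before and after the session | Q2 answers are candidates |
| Filter | Univariate p<0.1, correlation <0.6 | Neither condition concerns timing |
| Model | Influences on certain intention | Certain is defined only for the pre-intervention answer |

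No sentence limits the model's candidates to Q1 or baseline variables. None sets up a second model with post-intervention intention as its outcome.

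**2. Who is lost if a Q2 variable is retained.** Inputs: 2750 mothers (*Sample size*) and 1:1 allocation (*Design*). Controls without Q2: 2750 / 2 = 1375. A complete-case model drops all of them. The alternative is to impute a variable observed for no one in that arm.

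**3. What a consequence does when entered as a predictor.** All effects here are assumed. Let B be a genuine pre-intervention belief with coefficient 0.50 on the logit of certain intention Y. Let M be a later answer caused by Y and B, with M = 0.5·Y + 0.2·B + standard normal error. M has no effect on Y. By Bayes' rule:

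logit P(Y=1 | B, M) = constant + 0.50·B + 0.5·(M − 0.2·B)

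- coefficient of M: 0.5, although its causal effect on Y is zero
- coefficient of B: 0.50 − 0.5 × 0.2 = 0.40

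A simulation of this setting (300 runs, n = 1375) agreed. M was significant at 0.05 in 100% of runs, and the mean coefficient of B fell from 0.50 to 0.40. The size and direction of the shift depend on the assumed effects. The illustration shows how the error works and does not estimate its size in this trial.

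**4. Does the selection method add a separate problem?** With k unrelated, independent candidates, the chance of at least one p<0.05 is 1 − 0.95^k. Simulating the p<0.1 screen followed by backward selection at 0.05 on pure noise (300 runs, n = 1375, 75% certain, all assumed):

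| Candidates (assumed) | 1 − 0.95^k | Screen plus stepwise |
|---|---|---|
| 10 | 40% | 39% |
| 20 | 64% | 62% |
| 30 | 79% | 76% |

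The formula applies equally to a pre-set model with k null terms. On this measure the selection procedure is no worse than fitting every candidate at once.

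**The case against.** **It may be a drafting slip.** Shortly before, the same section compares intention measured before and after the session. Two parallel analyses, each intention with its own questionnaire, may have been compressed into one sentence. The model sentence does not repeat that intention is pre-intervention, and it names no Q2 variable. This is plausible, and it means that Q2 terms *may* enter, not that they will. The text as written still allows it and nothing elsewhere corrects it.

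**The list of independent variables may serve another model.** The abstract also plans logistic regression for determinants of coverage, and post-session opinions do precede that outcome. This stands, so the list is weak support and the point does not rest on it.

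**The imputation sentence is general.** It is not tied to this model or to Q2. This also stands: the article does not say that Q2 will be imputed for controls.

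**The analysis is exploratory.** It makes no treatment comparison, and the itemised list under *Study outcomes* does not include determinants of intention. This limits the weight of the point without removing it.

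**Stronger readings that a reader might infer.** One is that screening plus stepwise selection makes a false factor 64% to 87% likely (20 to 40 candidates). That range is 1 − 0.95^k for an assumed number of unrelated candidates. It holds for a pre-set model too, so it shows no harm from selection. Another is that effects will be biased away from zero. Nothing in the document supports this, and the one shift computed here runs toward zero. A third is that stepwise selection must be dropped. Statisticians differ on this for an exploratory model, and the article adds a correlation limit, a final collinearity check and two fit checks.

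**Conclusion.** The point holds in a limited form. Followed as written, the plan lets answers given after the session count as influences on an intention stated before it. A model that retained such an answer would be confined to the MI arm, at a cost of about 1375 controls, or would need values never observed in the control arm.

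This is conditional on a Q2 variable passing the filters. It concerns Q2 variables only, because Q1 and baseline variables raise no problem of time order. It affects a secondary, exploratory analysis and leaves the randomised comparison of coverage at 7 months untouched. The count of 1375 assumes an even split of the 2750 mothers and that controls completed Q1. The article restricts only Q2 to the MI arm.

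One minor remark on the entry rule: the p<0.1 filter does not guard against collinearity, although it is presented as doing so. Only the correlation limit addresses that.

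**What to change.** 1. Limit both the univariate screen and the logistic model for pre-intervention intention to baseline socio-demographic and clinical variables and Q1 answers, using mothers from both arms.
2. Analyse post-intervention intention and Q2 answers separately within the MI arm, adjusted for pre-intervention intention. Report the results as associations.
3. State the outcome of each model by time point, and label both analyses exploratory.
4. Optionally, attribute the control of collinearity to the correlation limit alone.

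The cost is a change of wording and one extra MI-arm analysis. No new data are needed.
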